### Study sample size for individually randomized designs

The trial is endpoint-driven, as the primary analysis for each vaccine arm versus the concurrent shared placebo/control arm is triggered by occurrence of a total of 150 cases of MARV disease across these two arms. The primary analysis results will be reported but blinded follow-up will still continue. We assume a 1% cumulative attack rate in the control arm over 6 months of outbreak time. The trial period could involve several years of follow-up and across outbreaks. As stated above, there will be two interim analyses at the points when 1/3 and 2/3 of events have occurred, respectively. We use the O'Brien-Fleming-type spending function for both false-positive and false-negative errors. All the sample size calculations were conducted using the R package *rpact*.

For example, with a target level VE of 60%, with 150 total endpoints in a pairwise comparison, there is approximately 90% power to reject VE less than or equal to 30% if true VE is 60%, based on a logrank test with one-sided type I error rate of 0.025. With equal allocation to the active vaccine arm and the control arm, a minimum follow-up of 3 months for the last accrued participant and an annual drop rate of 10%, we calculated sample sizes for different accrual rates (Table 1). If on average 30,000 participants will be accrued each month, we need 18,062 participants per arm and an expected study duration of 9.1 months. Lower accrual rates are associated with longer study durations but smaller sample sizes. Using the sample size of 18,062 per arm, we simulated 100 times exponentially distributed event times without early stopping to investigate the coverage of the two-sided confidence interval of the VE estimate. The average total number of events is 179 and the average 95% confidence interval for the VE is (45%, 71%). The lower confidence bound would exclude 30% with a probability of 0.93, and the point VE estimate is greater than 50% with a probability of 0.91. We performed a sensitivity analysis, varying the accrual rate, assuming a 1% cumulative attack rate in the control arm over a 12-month period with an annual dropout rate of 10%, and a minimum follow-up of 6 months after the last accrual (Table 1). The sample size increases with increasing accrual rate to about 18,062 participants per arm. The best sample size is about 20,000 participants per arm, or about 40,000 participants per vaccine/comparator combination.

**Table 1. table1-17407745221110880:** Required total sample size, expected study duration (in months).

Accrual rate(month)	Expected study duration(months of outbreak time)	Analysis times (months ofoutbreak time)			Cumulative total number of participants(both arms)		
		First interim	Second interim	Final	First interim	Second interim	Final
1000	14.4	9.4	13.3	16.7	9,370	13,350	13,721
5000	6.6	4.2	6.0	7.8	20,771	24,248	24,248
10,000	4.9	2.9	4.4	5.9	29,292	29,292	29,292
20,000	3.8	2.1	3.4	4.7	33,873	33,873	33,873
30,000	3.4	1.8	3.0	4.2	36,124	36,124	36,124

To reduce the time to obtain reliable insights about VE, the study size should be as large as possible. The large number of sites at diverse geographical locales will smooth out uncertainty in projected MARV disease attack rates in specific locales during specific calendar time periods. To increase the reliability of results, all efforts will be made to minimize the occurrence of missing data. The occurrence of and reasons for missing data will be reported by randomization group.

In the event that design 1.a. was used to assess the VE against infection by recruiting cohorts of people with potential high exposure, but in the absence of an outbreak, then the trial outcome could be infection measured by seroconversion against MARV. This design would involve serial blood samples from trial participants, with an infection event defined as a significant rise in antibody for bracketing serum samples. Since the time of infection would be interval-censored, analysis would be carried out using survival analysis for such data.^
14
^ Since the primary goal of vaccination would be to prevent disease, a VE estimate based only on infection, at best, would be likely to support only an accelerated/conditional approval that would require additional post-licensure effectiveness study(ies); and at worst, it would serve only as a hypothesis-generating demonstration project.

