## Results

### VE analysis

The primary efficacy endpoint will be analysed as a time-to-event outcome, including only those events that occur 10 days after the final vaccination dose. Such a gap of 10 days is chosen to allow time for the vaccination series to take effect and to reduce the chance of including events occurred prior to the vaccination due of the incubation period for Marburg. All participant-level failure (diagnosis with disease) and censoring events are reported relative to the time of randomization. The time of virologically confirmed (i.e. laboratory-confirmed) MARV disease is the earliest time of reported qualifying MARV disease symptoms that occur within 10 days of virological confirmation of MARV infection. Participants’ follow-up times will be right censored at the time of last contact at which endpoint status was assessed. Cox proportional hazards regression will be used for analysis. VE, measured by one minus the hazard ratio (vaccine versus placebo/comparator), will be the effect measure. Inference will be based on a one-sided logrank test of H_0_
^benefit^: VE ≤ 0.30, using an O'Brien-Fleming boundary for early termination that preserves an experimental (one-sided) 0.025 error rate; the alpha levels would be one-sided 0.0003 at 50 events and one-sided 0.0069 at 100 endpoints, where the remainder of the (one-sided) 0.025 error rate would be spent at the final analysis. Using these O'Brien-Fleming criteria after 50 and 100 events, benefit is established when estimated VE is ≥80% and ≥59%, and lack of benefit, that is, ruling out the target VE of 60% for which the trial has 90% power, is established when estimated VE is ≤−6% and ≤34%, respectively. When estimating VE against infection, the outcome would be infection as measured by time to seroconversion, using interval censoring methods for the estimand. In this case, the operating characteristics of the statistics would be the same as described above.

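### Table 1 counts every case from randomisation, but the primary endpoint starts 10 days after the last dose, so the tabled sample sizes and look times are optimistic for that endpoint

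*Protocol article*

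**What the plan says.** - **Endpoint.** Under VE analysis, the primary time-to-event analysis is described as "including only those events that occur 10 days after the final vaccination dose". The clock still starts at randomisation: "All participant-level failure (diagnosis with disease) and censoring events are reported relative to the time of randomization".
- **Sizing.** Under Study sample size for individually randomized designs: "We assume a 1% cumulative attack rate in the control arm over 6 months of outbreak time". The target is "approximately 90% power to reject VE less than or equal to 30% if true VE is 60"%, by a "logrank test with one-sided type I error rate of 0.025". Allocation is equal, minimum follow-up is 3 months and dropout is 10% a year. From these, "we calculated sample sizes for different accrual rates (Table 1"). No excluded early period is mentioned. The section ends by recommending about 20,000 per arm.
- **Trigger.** The primary analysis "is triggered by occurrence of a total of 150 cases of MARV disease across these two arms". Interim looks come at one third and two thirds of the events.
- **Doses.** The Methods foresee two-dose vaccines. No dosing interval is given.
- **Estimand.** The paragraph after the VE analysis text favours an intention-to-treat, treatment-policy estimand. It presents a post-vaccination counting window only as a possible variation.

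**The concern.** A participant contributes no primary endpoint until 10 days after the last dose. Under fast accrual, follow-up at the early looks is short, so the excluded window is a sizeable share of it. If Table 1 ignores the window, its look times, durations and N are too favourable for the endpoint as defined. The trigger wording adds a second risk. It speaks of cases of MARV disease, not of cases inside the counting window. Read literally, the final analysis could be called at 150 cases, some of which the primary analysis then discards.

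**Working it through.** **Inputs from the article.** Control hazard: −ln(0.99)/6 = 0.001675 per month. Vaccine hazard: 0.4 × 0.001675 = 0.000670 (VE 60%). Dropout hazard: η = −ln(0.90)/12 = 0.00878 per month. Accrual is uniform at r per month up to N, 1:1, and the final look is at N/r + 3 months.

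**Formula.** Let d be the delay from randomisation to the start of counting, and t the look time. Expected qualifying events are the sum over the two arms of

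(r/2) ∫ λ/(λ+η) × [exp(−(λ+η)d) − exp(−(λ+η)(t−s))] ds, with s from 0 to min(N/r, t−d).

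**Step 1: reproduce Table 1 (d = 0).** At 30,000 per month, N = 36,124 and t = 36,124/30,000 + 3 = 4.20 months. The control arm gives 106.9 events and the vaccine arm 42.9, in total 149.8. The other four rows also give 149.8 at N/r + 3. At the tabled, rounded times the five rows give 48.8–51.0, 99.2–100.3 and 148.5–150.0 events. Table 1 therefore contains no excluded period.

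**Step 2: apply the endpoint's window.** One dose at randomisation gives d = 10 days (0.329 months). For two doses I assume intervals of 28 and 56 days to show a range, so d = 38 or 66 days. Expected qualifying endpoints at the tabled looks:

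| Accrual per month | One dose | Two doses, 28 days (assumed) | Two doses, 56 days (assumed) |
|---|---|---|---|
| 1,000 | 46.6 / 94.1 / 144.2 | 37.4 / 80.7 / 129.5 | 29.3 / 68.5 / 115.0 |
| 5,000 | 43.2 / 90.2 / 139.1 | 25.0 / 64.3 / 113.2 | 11.8 / 41.6 / 87.5 |
| 10,000 | 38.3 / 87.9 / 137.6 | 15.7 / 56.6 / 106.2 | 3.1 / 28.3 / 75.2 |
| 20,000 | 36.4 / 87.0 / 137.0 | 8.4 / 50.8 / 100.8 | 0 / 17.3 / 64.9 |
| 30,000 | 36.5 / 86.4 / 135.7 | 5.3 / 47.8 / 97.1 | 0 / 11.9 / 58.8 |

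**Step 3: what restores the count.** At unchanged N, the looks come about 0.33–0.36 months later for one dose. In the 30,000 row they move to 2.12, 3.33 and 4.54 months. With 28 days they come about 1.3–1.4 months later.

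Alternatively, keep 3 months' minimum follow-up and raise N:

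| Accrual per month | Table 1 | One dose | 28 days | 56 days |
|---|---|---|---|---|
| 1,000 | 13,721 | 14,017 (+2.2%) | 14,884 (+8.5%) | 15,807 (+15.2%) |
| 10,000 | 29,292 | 31,036 (+6.0%) | 36,762 (+25.5%) | 43,919 (+49.9%) |
| 20,000 | 33,873 | 36,446 (+7.6%) | 45,484 (+34.3%) | 57,996 (+71.2%) |
| 30,000 | 36,124 | 39,212 (+8.5%) | 50,556 (+40.0%) | 67,489 (+86.8%) |

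**Step 4: the recommended 40,000.** At 30,000 per month and 3 months' minimum follow-up, 40,000 participants give about 153 qualifying endpoints for one dose, 111 for 28 days and 68 for 56 days.

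**Step 5: power under the literal trigger.** If all cases count towards 150, the evaluable number at the final look is close to that in Step 2. Fixed-design Schoenfeld power is Φ(ln(0.7/0.4) × √D/2 − 1.96). At D = 150: 0.5596 × 12.247/2 − 1.96 = 1.467, or 92.9%, which is compatible with the stated 90% once interim looks are added. One dose (D = 136 to 144.5) gives 90.4% to 92.0%. Two doses 28 days apart (D = 97 to 130) give 79% to 89%.

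**The case against.** The strongest reply is that the trial is event-driven. Looks are held at event counts, and Table 1's months are forecasts. This stands: if only qualifying endpoints are counted, no look takes place with 36 of them. It is simply held later, and the boundaries and the power at 150 are untouched.

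Second, the recommended 40,000 already exceeds the corrected one-dose N of about 39,200. This also stands for one dose. It does not stand for two doses under fast accrual: at an assumed 28 days the need exceeds 40,000 at 20,000 per month and above, and at 56 days already at 10,000 per month.

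Third, the article uses cases, events and endpoints interchangeably, so the trigger may well mean primary endpoints. That is the natural intention, but nothing in the text restricts the count to the window.

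Fourth, Table 1 is consistent with the intention-to-treat estimand that the article itself favours. This is true. But the VE analysis text states the restriction as the primary analysis, so the two paragraphs need reconciling.

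A reader might infer that every look would have far too few endpoints, or that the trial is underpowered. The documents do not support this. For one dose the final shortfall at the tabled times is about 4–10%. The large two-dose figures need an interval that the article does not state, and any power loss also needs the literal reading of the trigger.

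**Conclusion.** The point holds as an inconsistency between the printed table and the printed endpoint. Table 1 is reproduced when every case from randomisation counts, so its N, durations and look times are optimistic for the endpoint as defined. For one dose the effect is modest: about 0.35 months of delay, or 2% to 8.5% more participants, with only the first look under fast accrual clearly short (about 36 of 50). For two doses it can be large, with about 97–130 final endpoints at an assumed 28 days and 59–115 at 56 days.

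The stated power and the boundaries are safe on condition that only qualifying endpoints trigger the looks. The figures assume constant hazards, uniform accrual and the first dose at randomisation. Any gap between randomisation and first dose would add to the delay.

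**What to change.** 1. Reconcile the VE analysis text with the estimand paragraph that follows it, and state which events the primary analysis counts. If it is all events from randomisation, Table 1 can stand.
2. If the post-vaccination window is kept, re-run the rpact calculation with that delay for one-dose and two-dose schedules, state the interval assumed for sizing, and restate Table 1 and the recommended N.
3. In the Methods and in the sample size section, say that only endpoints inside the counting window count towards 50, 100 and 150.

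The cost is a re-run of an existing calculation and a few sentences. The stated durations or sample sizes become less favourable. The test, the boundaries and the 150-endpoint target do not change.

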## Methods

### Operating characteristics of the trial design

A core protocol approach will be used, allowing multiple vaccine candidates to be tested against a shared placebo/control group. The primary objective of the trial will be to evaluate the effect of each vaccine on the rate of virologically confirmed MARV disease, regardless of severity. In some cases, it may also be possible to evaluated MARV infection as a co-primary outcome. Although the study may lack power for formal statistical inference about VE against severe disease or death due to MARV disease, these secondary endpoints will be evaluated and reported for each vaccine. Additional exploratory endpoints will include VE between the first and second dose, for two-dose vaccines. Infecting viruses will be sequenced as much as possible to assess the influence of virus clades and evolution on transmissibility, virulence and VE. A subset of trial participants will provide periodic blood samples. Immune markers measured from participants in this immunogenicity subset will be used to assess immune correlates of risk and protection, and help with the assessment of VE against infection.

The trial is endpoint-driven, as the main analysis for each vaccine arm versus the concurrent shared placebo/control arm is triggered by the occurrence of a total of 150 cases of MARV disease across these two arms. While results from the main analysis will be reported, blinded follow-up will continue to evaluate safety and duration of immunity. This fixed number of 150 endpoints provides 90% power to rule out the hypothesis that VE is ≤ 30%, when the true VE is ≥ 60%, where statistical significance would be achieved if the estimated VE were ≥ 50%. In the setting of COVID-19 vaccines, such results would meet or exceed the World Health Organization-Food and Drug Administration (FDA) established threshold for worthwhile VE.

A global data monitoring committee will regularly review the accumulating safety results and major endpoint results. Different candidate vaccines may be available or suitable to enter the trial at different calendar times. Using a shared placebo/control group and a common core protocol to evaluate multiple candidate vaccines in the trial, resources allocated to the evaluation of each candidate vaccine will be judiciously saved while a high standard of scientific rigour and efficiency is ensured.^
10

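### The simulated interval and success probabilities come from an average of 179 events, while the primary analysis is triggered at 150, so they are somewhat too favourable for that analysis

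*Protocol article*

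**What the plan says.** The article fixes the amount of information at the primary analysis in two places. Under Methods, *Operating characteristics of the trial design*, "the main analysis for each vaccine arm versus the concurrent shared placebo/control arm is triggered by the occurrence of a total of 150 cases". Under Results, *Study sample size for individually randomized designs*, the analysis is again "triggered by occurrence of a total of 150 cases of MARV disease across these two arms". Blinded follow-up continues afterwards.

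The second section claims "approximately 90% power to reject VE less than or equal to 30% if true VE is 60%, based on a logrank test with one-sided" error of 0.025. It derives 18,062 per arm for accrual of 30,000 per month, with these inputs: "We assume a 1% cumulative attack rate in the control arm over 6 months of outbreak time"; "With equal allocation to the active vaccine arm and the control arm, a minimum follow-up of 3 months for the last accrued participant"; and 10% annual dropout.

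It then describes a simulation: "Using the sample size of 18,062 per arm, we simulated 100 times exponentially distributed event times without early stopping". The result is: "The average total number of events is 179 and the average 95% confidence interval for the VE is (45%, 71" (upper limit 71%). The two probabilities are 0.93 (lower limit above 30%) and 0.91 (estimate above 50%). The article does not comment on the difference between 179 and 150, gives no simulated result at 150 events, and reports no Monte Carlo error.

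**The concern.** An event-driven analysis has the precision of its event count. If the count at the primary analysis is 150, an interval and success probabilities from an average of 179 events belong to a later data cut. Leaving out early stopping does not explain the gap: without the looks at 50 and 100 events, the final analysis is still at 150.

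The two simulated probabilities correspond to the article's success rule (estimate above 50%, true efficacy below 30% ruled out). A reader would take 0.93 as the chance that the planned analysis excludes 30%, and (45%, 71%) as its expected precision. Both are more favourable than 150 events support.

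**Working it through.** **Inputs from the article.** True VE 60% (hazard ratio 0.4); null VE 30% (hazard ratio 0.7); 1:1 allocation; D = 150 at the trigger and 179 in the simulation; two-sided 95% interval; 100 replicates.

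**Method.** With equal arms and rare events, cases split about 0.4 : 1 between vaccine and control, so d1 = D × 0.4/1.4 and d0 = D − d1. Then:

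- SE(log HR) = √(1/d1 + 1/d0)
- VE limits = 1 − 0.4 × exp(±1.96 × SE)
- P(lower limit > 30%) = Φ(ln(0.7/0.4)/SE − 1.96), with ln(0.7/0.4) = 0.5596
- P(estimate > 50%) = Φ(ln(0.5/0.4)/SE), with ln(0.5/0.4) = 0.2231

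**Step 1: reproduce the stated figures at D = 179.** d1 = 51.1, d0 = 127.9, SE = 0.1655.

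- Interval: (44.7%, 71.1%); stated (45%, 71%).
- P(lower limit > 30%) = Φ(3.382 − 1.96) = 0.923; simulation gives 0.933 to 0.938; stated 0.93.
- P(estimate > 50%) = Φ(1.349) = 0.911; stated 0.91.

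**Step 2: repeat at D = 150.** d1 = 42.9, d0 = 107.1, SE = 0.1807.

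- Interval: (43.0%, 71.9%), 28.9 points wide against 26.4 at 179 events.
- P(lower limit > 30%) = Φ(3.096 − 1.96) = 0.872.
- P(estimate > 50%) = Φ(1.235) = 0.892.

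**Step 3: check by simulation at 150 events.** A conditional binomial split (1,000,000 draws) gives 0.884 for both probabilities. A survival simulation with 18,062 per arm, accrual of 30,000 per month and 10% annual dropout (3,000 runs) gives 0.893 for both. The average interval is about (42.5%, 71.7%).

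The two probabilities coincide because of one outcome. A 50:100 split gives an estimate of exactly 50% and a Wald lower limit of 1 − 0.5 × exp(1.96 × √(1/50 + 1/100)) = 29.8%, so it narrowly fails both strict criteria. If exactly 50% counts as success, as in *Operating characteristics of the trial design*, the binomial probability is 0.915.

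**Step 4: which event count belongs to 18,062 per arm?** Accrual takes 36,124/30,000 = 1.2 months. The control hazard is −ln(0.99)/6 = 0.001675 per month and the vaccine hazard 0.4 times that. Integrating over uniform entry with 10% annual dropout gives 149.6 expected events at 4.2 months, the final analysis time in Table 1 for this accrual rate. At 5 months the expected count is 182, so 179 events would need about 5 months. Table 1 prints no event counts; its timing agrees with 150.

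**Step 5: Monte Carlo error with 100 replicates.** √(0.93 × 0.07/100) = 0.026 and √(0.91 × 0.09/100) = 0.029. The 95% ranges are about 0.88 to 0.98 and 0.85 to 0.97.

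**Step 6: the separate power claim at 150 events.**

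- Schoenfeld, fixed design: Φ(√(150/4) × 0.5596 − 1.96) = 0.929
- Schoenfeld with O'Brien-Fleming looks: 0.918
- Null-hypothesis variance: 0.903
- Unequal-event Wald variance: 0.872 fixed, 0.887 by binomial simulation with the looks

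These lie around the stated figure of about 90%.

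**The case against.** The best defence is that nothing in the design rests on this simulation. The trigger, error rate, power and sample size come from a separate logrank calculation, which step 6 does not overturn. The simulation's declared purpose was interval coverage, and the article openly states the 179 events, the 100 replicates and the absence of early stopping. The differences are small: about 2 points on the lower limit and, by simulation, 0.93 to about 0.88 or 0.89. The 0.91 does not fall if exactly 50% counts as success.

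All of that stands and limits the size of the point. It does not remove it. The figures are presented as properties of this design, and no text tells the reader that they apply to more events than the primary analysis will have.

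A reader might infer more than the article supports:

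- **That the trial is underpowered, or that this is its only power check.** It is not. The Wald interval is a stricter criterion here than a balanced-variance logrank test, whose final boundary is about 1 − 0.7 × exp(−2.004 × 2/√150) = 49.5%.
- **That few replicates inflated the results.** They add noise only. The stated values agree with the analytic ones at 179 events.
- **That a larger trial was simulated, or that the trial stops at 150 events.** The sample size is the same 18,062 per arm, the simulation simply holds more events, and follow-up continues after the primary analysis.

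**Conclusion.** The point holds as a correction to reported operating characteristics. At the 150-event trigger with true VE 60%, the 95% interval is about (43%, 72%) rather than (45%, 71%). The probability that its lower limit exceeds 30% is about 0.87 to 0.89 rather than 0.93. The probability of an estimate above 50% is about 0.88 to 0.89, or 0.915 under the at-least-50% wording, so the 0.91 hardly changes. The claim of about 90% power at 150 events is left standing.

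These values assume proportional hazards, equal arms, rare events and no interim stopping, as in the article's own simulation. Within the 0.87 to 0.89 range, the lower end is the normal approximation and the upper end the simulations.

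Why the simulation reached 179 events cannot be settled from the article. One possibility is a different rate or a calendar cut-off. The text says "we need 18,062 participants per arm and an expected study duration of 9.1 months", while Table 1 gives 3.4 months expected and 4.2 at the final analysis. A control rate of 1% per 12 months followed to 9.1 months yields about 173 events. That is inference only, and the conclusion does not depend on it.

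**What to change.** Re-run the simulation with each replicate cut at its 150th event, under the stated accrual and dropout and without early stopping, as now. Use several thousand or more replicates and report the Monte Carlo error. Replace the interval and both probabilities with the results, and say whether an estimate of exactly 50% counts as success. A run with the looks at 50 and 100 events is optional and should be reported separately, because the 150-event values given here do not include those looks.

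At minimum, state that the present figures apply to an average of 179 events and add the 150-event values beside them.

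The cost is minutes of computing and slightly less favourable stated figures. The trigger, sample size and conduct of the trial do not change.

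### The attack-rate sensitivity analysis repeats the base-case 18,062 per arm and cites a table holding only the base case; at 30,000 per month its assumptions need about 19,800 per arm

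*Protocol article*

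**What the plan says.** All of this is in the protocol article, Results, under the heading on sample size for individually randomized designs.

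- **Base case.** "We assume a 1% cumulative attack rate in the control arm over 6 months of outbreak time". The primary analysis is "triggered by occurrence of a total of 150 cases of MARV disease across these two arms", allocation is equal, and there is "a minimum follow-up of 3 months for the last accrued participant and an annual drop rate of 10" percent. At 30,000 participants per month the article gives 18,062 per arm.
- **Sensitivity analysis.** Accrual is varied again, "assuming a 1% cumulative attack rate in the control arm over a 12-month period with an annual dropout rate of 10" percent, now with 6 months' minimum follow-up. Table 1 is cited as the source, and the result is: "The sample size increases with increasing accrual rate to about 18,062 participants per arm".
- **Table 1.** The caption, "Required total sample size, expected study duration (in months"), names no scenario. There is one block of five rows, for 1,000 to 30,000 participants per month. The last row has 36,124 in total, which is 2 × 18,062.
- **Recommendation.** The section ends by recommending about 20,000 per arm.

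**The concern.** Two analyses that differ in attack rate and in minimum follow-up end in the same five-digit number and point to the same single-block table. Halving the event rate and doubling the follow-up partly offset each other, so similar totals would not be surprising. Identical totals at the same accrual rate would be.

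The attack rate is the least certain planning input, and the section itself acknowledges uncertainty in projected attack rates. If the sensitivity result is a carried-over base-case figure, the reader has no information on size or duration under the lower rate. The reader may also conclude that the required size hardly depends on it.

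**Working it through.** **Inputs (all from the section).** 150 events in total; true VE 60%, so hazard ratio 0.40; equal allocation; dropout 10% per year. Base case: 1% over T = 6 months, minimum follow-up F = 3 months. Sensitivity case: T = 12, F = 6. Assumed here: exponential event and dropout times, and uniform accrual at rate r.

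**Formulas.**

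- Control hazard λ = −ln(0.99)/T: 0.001675 per month (base), 0.000838 (sensitivity). Vaccine hazard is 0.4λ.
- Dropout hazard η = −ln(0.90)/12 = 0.00878 per month.
- Accrual time A = N/r; final analysis at A + F.
- Event probability for an arm with hazard h, with k = h + η: P(h) = (h/k) × [1 − (e^(−kF) − e^(−k(F+A)))/(kA)].
- Expected events = (N/2) × [P(λ) + P(0.4λ)]. Solve for N.

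**Step 1: reproduce Table 1.** The event target that returns the 30,000-per-month row is 149.8, in effect the stated 150. With the base-case inputs:

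| Accrual per month | Table 1 final N | Model N | N/r + 3 (months) | Table 1 final time |
|---|---|---|---|---|
| 1,000 | 13,721 | 13,722 | 16.72 | 16.7 |
| 5,000 | 24,248 | 24,249 | 7.85 | 7.8 |
| 10,000 | 29,292 | 29,293 | 5.93 | 5.9 |
| 20,000 | 33,873 | 33,875 | 4.69 | 4.7 |
| 30,000 | 36,124 | 36,127 | 4.20 | 4.2 |

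Every row is the base case. Without any model, final times of 5.9, 4.7 and 4.2 months cannot follow a minimum follow-up of 6 months.

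**Step 2: sensitivity case, same code and event target.**

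| Accrual per month | Total N | Per arm | Final analysis (months) |
|---|---|---|---|
| 1,000 | 18,270 | 9,135 | 24.3 |
| 5,000 | 29,740 | 14,870 | 11.9 |
| 10,000 | 34,350 | 17,175 | 9.4 |
| 20,000 | 38,000 | 19,000 | 7.9 |
| 30,000 | 39,590 | 19,795 | 7.3 |

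With exactly 150 events the last row is 19,821 per arm. With no dropout it is still about 19,300. The excess over 18,062 is 19,795/18,062 − 1 = 9.6% (9.7% with exactly 150 events).

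**Step 3: what 18,062 per arm delivers under the sensitivity inputs.** At 30,000 per month, A = 36,124/30,000 = 1.204 months. With F = 6, P(λ) = 0.005357 and P(0.4λ) = 0.002146. Expected events = 18,062 × (0.005357 + 0.002146) = 135.5, against 150. At Table 1's printed final times, the lower rate gives about 75 events in every row.

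**The case against.** Four points deserve weight.

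1. **The inputs offset each other.** Apart from dropout, halving the hazard and doubling the follow-up at 15,000 per month is the base case at 30,000 per month on a doubled time scale. A similar N is therefore expected, and the article never says outright that N is insensitive to attack rate. This is true, but the equality arises at about half the accrual rate, not at the same one.

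2. **No separate accrual range is given for the sensitivity run.** Under its assumptions, 18,062 per arm is right at about 13,600 per month. That rate is listed nowhere, and the text refers the accrual variation to Table 1, whose top rate is 30,000. What stands is that 19,800 is conditional on 30,000 per month and should be labelled so.

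3. **The misprint may lie elsewhere.** The same paragraph gives an expected duration of 9.1 months at 30,000 per month, where Table 1 has 3.4, so versions may have been mixed. The wrong element could be the assumptions or the citation rather than the number. This stands, and the remedy allows for it.

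4. **The consequence is small.** Analysis is triggered by events, so with 18,062 per arm the 150 events would come at about 7.9 months, with no loss of power. The recommended 20,000 per arm gives about 151 events in the sensitivity case at 30,000 per month. Both statements are correct. They limit the severity but do not make the reported figure follow from its inputs.

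**Conclusion.** The concern holds. Table 1 contains only the base case, its citation for the sensitivity analysis leads to results that are not there, and 18,062 per arm does not follow from the sensitivity inputs at any accrual rate in the table.

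At 30,000 per month the requirement is about 19,800 per arm, roughly 10% more, with the final analysis at 7.3 months against the 4.2 printed for the base case. The effect on duration is also marked at slow accrual: 24.3 months against 16.7 at 1,000 per month. These figures rest on exponential event and dropout times, uniform accrual, VE of 60% and about 150 events, a model that reproduces the article's own table.

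This is a reporting error that should be corrected. It does not undermine the event target, the error rates, the decision rules or the recommended 20,000 per arm.

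**What to change.** - Add the five sensitivity rows as a second block of Table 1, and label each block with its attack rate and minimum follow-up.
- In the sensitivity sentence, replace 18,062 by about 19,800 per arm at 30,000 per month. Keep 18,062 for the base case only.
- If the intended sensitivity inputs or accrual rates were different, correct those instead, so that inputs, table and sentence agree.
- Tie the recommended 20,000 per arm to the sensitivity case. At present both reported analyses give 18,062, and nothing shown leads to 20,000.

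The cost is one re-run of existing code, one table block and two edited sentences. The design does not change.
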